#### Outcomes

Univariable regression and multivariable regression analyses will be conducted using stepwise backward selection. For the primary outcome (ie, unplanned readmissions up to 30 days after surgery), we will conduct logistic regression analyses. For continuous secondary outcomes, we will use linear regression analyses; for dichotomous outcomes, we will use logistic regression analysis. We will use a general linear mixed model to analyze differences in sleep quality, DOS scores, and AMEXO scores over 5 days after the operation (Table 1). If a difference is observed, a post hoc power analysis will be used to examine which time point differs significantly. A 2-sided *P* value ≤.05 will be considered statistically significant. A 95% CI for the beta coefficient (β) will be calculated.

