### Outcomes

The primary patient outcome is the number of unplanned readmissions up to 30 days after surgery (Table 1). Secondary outcomes include the total number of complications at 30 and 90 days after surgery and the number of complications sensitive to fundamental care activities (eg, pneumonia, urinary tract infection, wound infection, deep vein thrombosis, malnutrition, and delirium) at 30 and 90 days after surgery. These data will be collected from patient records, and complications will be classified according to the revised version of the Clavien-Dindo classification system [37]. Secondary outcomes also include emergency department visits, ICU admissions up to 30 and 90 days after surgery, and hospital length of stay. Furthermore, patients’ QoL will be measured using the EQ-5D-5L [38], and the level of anxiety and depression in patients will be measured using the Hospital Anxiety and Depression Scale (HADS; Table 1) [39,40]. Patient satisfaction with care and sleep quality will be measured using the numeric rating scale (NRS) ranging from 0 to 10, with higher scores indicating higher satisfaction or sleep quality (Table 1). Sleep quality will be assessed once a day, from the first day after surgery until 5 days after the operation. In addition, the amount of home care (in hours per week) after discharge will be measured (Table 1). The risk screening scores routinely measured during hospital admission will be collected, ie, the Short Nutritional Assessment Questionnaire score (SNAQ) [41], the Delirium Observation Scale score (DOS) [42], the Braden scale [43], the Amsterdam UMC Extension of the John Hopkins Highest Level of Mobility scale score (AMEXO) [44] and the John Hopkins Fall Risk Assessment (JHFRAT; Table 1) [45].

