### Sample Size

The sample size is based on the primary objective of evaluating the effects of the FIP on unplanned readmissions. In our pilot study, we found an absolute reduction of unplanned readmission rates of 15% [16] and considered this 15% reduction of unplanned readmissions as clinically relevant, representing a readmission rate of 20% in the intervention group and 35% in the usual care group. To detect a 15% reduction in readmission rates at a 5% significance level (α) and a power of 80% (1 – β), a sample size of 136 patients per group is necessary, using a continuity-corrected chi-square test. We assume a 10% to 20% loss to follow-up (ie, not completing the questionnaires), and to compensate for this, the total sample size per group will be at least 150. Loss to follow-up is expected owing to the use of repeated questionnaires, which may burden patients. Recruitment ends as soon as both the groups have included 150 patients. To minimize attrition, we will collect detailed contact information and offer patients alternative data collection methods such as paper-based questionnaires if patients do not have an email address [52].

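### Questionnaire outcomes collected at baseline and three later times are given linear regression with no prespecified baseline term, so baseline gaps in this preference-allocated cohort can carry into the follow-up comparisons

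*Protocol article*

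**What the plan says.** Under Statistical Methods, Outcomes, the protocol article assigns models by outcome type: "For continuous secondary outcomes, we will use linear regression analyses; for dichotomous outcomes, we will use logistic regression analysis". One exception follows, a "general linear mixed model to analyze differences in sleep quality, DOS scores, and AMEXO scores" over the first 5 postoperative days. Univariable and multivariable regressions use backward stepwise selection.

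The Overview of Statistical Methods sets the adjustment rule. Patients' baseline characteristics are tested for differences between arms, and confounders are adjusted for if differences appear. The threshold given under Outcomes is "A 2-sided *P* value ≤.05 will be considered statistically significant".

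Table 1 schedules EQ-5D-5L and HADS for patients, and CSI+, self-rated burden and CarerQoL-7D for caregivers, at T0, at discharge, and at 30 and 90 days. Perseverance time has no T0 value.

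The Outcomes section words complications as a number: "Secondary outcomes include the total number of complications at 30 and 90 days after surgery". No count model is named.

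**The concern.** The questionnaires have the classic repeated-measures layout, one baseline and three follow-ups, yet the repeated-measures model goes to three ward measures instead. What remains for the questionnaires is linear regression whose baseline term depends on a significance test and then on a selection algorithm.

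In a randomised trial this would mainly cost precision. Here the Allocation section lets patients and families choose their group, and the caregiver criteria require willingness to give at least 8 hours of care a day. Families who accept may differ beforehand in strain, anxiety or quality of life. The Discussion itself treats comparison of prognostic variables between the groups as essential.

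Caregiver outcomes are the most exposed. The Discussion hypothesises benefit without added caregiver burden, and a baseline difference in burden could create or hide exactly that result.

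**Working it through.** **The plan's own figures.** None is given for the secondary analyses. The Sample Size section covers the primary outcome only ("representing a readmission rate of 20% in the intervention group and 35% in the usual care group") and states no SD, correlation or expected baseline gap for a questionnaire. I take from the document 150 per group, the two-sided 5% level, and the 10% to 20% questionnaire loss, which leaves 150 × 0.90 = 135 to 150 × 0.80 = 120 per group. The baseline gap *d* (0.1 to 0.3 SD) and the baseline-to-follow-up correlation *r* (0.3 to 0.7) are assumptions.

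**Step 1: how the T0 score could enter.**
- Patient scores (EQ-5D-5L, HADS): through the baseline test, if they count as baseline characteristics. The patient list under Data Collection Methods does not include them.
- Caregiver scores (CSI+, self-rated burden, CarerQoL-7D): the testing rule names patients only, so no route is stated.
- In either case backward selection may follow. No text fixes the T0 score as a covariate.

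**Step 2: how often the test would flag a true gap.** With 150 per group the standardised gap is *d* × √(150/2) = 8.66*d*, and power ≈ Φ(8.66*d* − 1.96) + Φ(−8.66*d* − 1.96):
- *d* = 0.1: 0.87, flagged about 14% of the time
- *d* = 0.2: 1.73, about 41%
- *d* = 0.3: 2.60, about 74%

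**Step 3: what an omitted T0 score leaves behind.** With no true effect, the expected follow-up difference is *r* × *d*. The chance of a significant result is Φ(b − 1.96) + Φ(−b − 1.96), with b = *r* × *d* / √(2/n). At n = 150 per group, √(2/150) = 0.1155.

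| *r* | *d* = 0.1 | *d* = 0.2 | *d* = 0.3 |
|---|---|---|---|
| 0.3 | 0.03 SD, 6% | 0.06 SD, 8% | 0.09 SD, 12% |
| 0.5 | 0.05 SD, 7% | 0.10 SD, 14% | 0.15 SD, 26% |
| 0.7 | 0.07 SD, 9% | 0.14 SD, 23% | 0.21 SD, 44% |

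At 120 per group the percentages run from 6% to 37%.

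The table describes an outcome whose T0 score is left out regardless of any test. Where a T0 score is tested and not flagged, the gap observed in the sample is at most about 1.96 × 0.1155 = 0.23 SD, so the carry-over is at most about 0.7 × 0.23 = 0.16 SD. For caregiver scores, with no test named, the full range applies.

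**Step 4: precision.** Including T0 multiplies the standard error by √(1 − *r*²): 0.95 at *r* = 0.3, 0.87 at 0.5, 0.71 at 0.7.

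**The case against.** The best defence is that silence is not exclusion. The article prescribes multivariable regression and confounder adjustment, and a condensed article may leave covariate lists to an analysis plan. If the T0 score is a candidate in backward selection it would almost always survive: at *r* = 0.5 and 300 patients, t ≈ 0.5 × √298 / √0.75 ≈ 10. That stands, and so it cannot be said that these outcomes are analysed without their baseline value. It does not cover scores that never become candidates, and the stated rule gives caregiver scores no route in.

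Three stronger readings are tempting and should not be made.
- **Wrong error bars.** A separate linear regression at each visit has a valid, if less precise, standard error. It would be wrong if visits were stacked as independent rows, which the article does not propose. Nor do counts rescue this reading: in simulations with 150 per group (assumed mean of 0.8 complications, or 0.8 versus 0.5, and negative binomial dispersion of 0.5 to 2), linear regression kept type I error at 4.9% and interval coverage at 94.7% to 95.2%.
- **No suitable model for complications.** The primary outcome is also worded as a number yet is analysed by logistic regression, so complications may likewise be meant as yes/no. This is an ambiguity, not a stated error.
- **Patients dropped for a missed visit.** Handling of Missing Data names multiple imputation, with complete cases as a sensitivity analysis. Its 40% thresholds contradict each other, but that is a separate matter, and complete-case analysis is not fixed as the main approach.

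A further fair point is that T0 may not be a clean baseline. Table 2 gives intervention families the app one week before admission. Data Collection Methods puts baseline questionnaires on the day of admission, whereas Table 2 puts baseline questionnaires within 24 hours after surgery. A score taken after group choice and first exposure could absorb some early effect, so its timing has to be settled.

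**Conclusion.** The point holds as a weakness in how baseline adjustment is fixed for secondary outcomes. The T0 score is collected, but its use is left to a test that would miss a 0.2 SD gap about 59% of the time (100% − 41%) and that does not name caregivers at all. If T0 is left out, the spurious difference is 0.03 to 0.21 SD over the assumed ranges, and type I error is about 6% to 44% at 150 per group. These sizes rest wholly on assumed gaps and correlations; the article gives neither. A real gap is plausible because groups are self-selected, but it is not shown. The primary analysis of readmissions is untouched.

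**What to change.** - State that the T0 score is a covariate in every model for an outcome that has one, for patients and caregivers alike, whatever the baseline tests show and outside backward selection.
- Extend the mixed model to EQ-5D-5L, HADS, CSI+, self-rated burden and CarerQoL-7D, with all follow-up visits as outcomes and a group-by-visit term.
- Reconcile the time at which T0 is taken between Data Collection Methods and Table 2, and say how it relates to app access.
- As a minor clarification, say whether complications are analysed as counts (negative binomial or robust standard errors) or as yes/no. A plain Poisson model should be avoided: its coverage was only 78% to 91% in the same simulations.

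The cost is a few sentences and some extra analysis work. Table 1 already schedules the scores, so no new data are needed.

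### The plan names a post hoc power analysis to find which postoperative day differs for sleep quality, DOS and AMEXO, but a power analysis cannot locate a difference

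*Protocol article*

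**What the plan says.** The Outcomes subsection of Statistical Methods commits to a "general linear mixed model to analyze differences in sleep quality, DOS scores, and AMEXO scores" over the 5 days after the operation. The next sentence covers what follows a positive result: "a post hoc power analysis will be used to examine which time point differs significantly". Two general statements close the paragraph: "A 2-sided *P* value ≤.05 will be considered statistically significant" and "A 95% CI for the beta coefficient (β) will be calculated". The paragraph names no other procedure for the day-level question.

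On timing, the Outcomes section of Methods is explicit for one of the three measures: "Sleep quality will be assessed once a day, from the first day after surgery until 5 days after the operation". For DOS and AMEXO, Table 1 marks the 5-day postoperative period (T1) but gives no daily frequency.

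**The concern.** The stated aim is inferential: to declare that the groups differ significantly at particular time points. The stated tool is not an inferential procedure for that aim. A power analysis gives the probability that a test would reject under some effect size. It does not estimate the difference between the family involvement program (FIP) and usual care on a given day, and it does not test that difference.

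This is a stated procedure that does not fit its stated purpose, so it is not a detail that an article may leave to a fuller document. An analyst who follows the sentence literally can make no valid statement about any day. One who sets it aside has to choose the comparison after seeing the data: FIP against usual care on each day, or day against day within a group, with or without adjustment for several tests. The results at stake are the day-specific findings on sleep, delirium screening and mobility.

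**Working it through.** The protocol gives no figure for this step, so there is nothing to reproduce. The check is whether a post hoc power analysis could answer the question, and what would follow if it were replaced by day-level tests.

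**Inputs**
- Two-sided significance level .05 (Statistical Methods, Outcomes).
- Five daily assessments for sleep quality (Methods, Outcomes). For DOS and AMEXO, five is an assumption.
- Day-level follow-up only after an overall difference is seen (Statistical Methods, Outcomes).

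**Step 1. Power from the observed effect.** For a two-sided z test at .05, let z_p be the absolute z value that corresponds to the P value. Then

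observed power = Φ(z_p − 1.96) + Φ(−z_p − 1.96).

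| P value | Observed power |
|---|---|
| .001 | 0.908 |
| .01 | 0.731 |
| .05 | 0.500 |
| .20 | 0.249 |
| .50 | 0.104 |

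The only input that varies is the P value. Observed power for a day therefore presupposes that a test for that day has already been done, and it adds nothing to that test.

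**Step 2. Power from an assumed effect.** If the effect is assumed, power depends on that effect, the variability, the number of patients and the significance level. The observed group difference does not enter, so the result cannot show on which day the groups differed.

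Under either reading the output is a probability of rejection. It is not a day-specific estimate, test or confidence interval.

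**Step 3. What day-level tests would need in its place.** Treat the overall result as a test at .05 that must be passed first.
- No day differs: a false day-level claim first requires a false-positive overall test, so the familywise error is held near 5% per outcome, with or without adjustment of the daily tests.
- One of five days truly differs, and the overall test is passed because of it: the other four days are tested at .05 each. Under independence the chance of at least one false claim is 1 − 0.95^4 = 1 − 0.8145 = 0.185, or about 18.5%. Positive correlation between days in the same patients lowers this.

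The gate therefore protects in the first case and not fully in the second. Holm's procedure covers the second: with five days, the smallest P value is compared with .05/5 = .01, the next with .05/4 = .0125, and so on.

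**The case against.** The strongest reply is that this is a slip of one word. Delete the word for power and an ordinary post hoc analysis of time points remains, next to a stated significance level and a planned 95% CI. That is probably what was meant, and it bears on how serious the point is. It does not settle it: the shortened sentence would still not say which comparison is made at each time point, and the text as it stands cannot be carried out for its purpose.

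Two stronger readings are tempting, and the document supports neither.

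- A reader might infer that the whole time-course question for sleep, delirium and mobility goes unanswered. It does not. The mixed model can still show whether the groups differ over the 5 days.
- A reader might infer that the plan carries the error of ungated daily testing, 1 − 0.95^5 = 22.6% per outcome or 1 − 0.95^15 = 53.7% over three outcomes. These figures do not describe the plan. The follow-up is conditional on an overall difference, and the text does not say that day-level tests will be unadjusted. Daily assessment is stated only for sleep quality, so a count of fifteen tests is itself partly assumed.

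It is also fair to say that the lack of a multiplicity rule for secondary contrasts would not be a finding by itself, since an article may leave that to the analysis plan. It comes in here only because the replacement sentence should be complete.

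**Conclusion.** The point holds in a narrow form. The plan assigns the question of which day differs to a procedure that cannot answer it. This follows from what a power analysis is, and it rests on no assumption about the data.

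The reach is limited to a conditional follow-up step for three secondary measures. The overall mixed-model comparison stands, and so does the primary analysis of unplanned readmissions. The wording should be corrected, but the study's main conclusion does not depend on it.

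The figure of 18.5% is a reason to adjust the replacement contrasts and not a measure of error in the present text. It assumes five assessed days, one true difference, an overall test that is passed, and independence between days.

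**What to change.** Delete the post hoc power analysis and put this in its place:

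> The mixed model will include group, day and group-by-day terms. The overall group difference over the 5 days will be reported. If the joint test of group and group-by-day is significant, FIP versus usual care differences at each assessed day will be estimated as model contrasts with 95% CIs and Holm-adjusted P values within each outcome.

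The gate should be the joint test and not the interaction alone. A benefit of constant size on all days produces no interaction, so an interaction-only gate would keep the day-level results from being shown in just that case. The phrase on each assessed day leaves room for DOS and AMEXO, whose frequency within the 5 days is not stated. Holm within each outcome does not control error across the three outcomes.

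The cost is one sentence. The measurements and the mixed model are already planned, and no further patients or data are needed. The Results section reports that follow-up ended in May 2022, but this is purely an analysis step, so it can still be corrected in the analysis plan or stated in the report.

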#### Additional Analyses

In this study, some additional analyses will be performed. We will analyze whether performing one or more optional care activities (Textbox 2) and the involvement of multiple family caregivers per patient can modify patient outcomes. Furthermore, in a sensitivity analysis, we will compare outcomes from patients in the FIP study arm to those from the comparison group whose family caregivers decline to participate in the FIP. The analysis will be based on intention-to-treat principles, meaning that every patient and family caregiver will be analyzed in the group that they chose before surgery.

#### Handling of Missing Data

If >40% of the missing data in the data set occur, multiple imputation by the chained equations method in R will be used [59,60]. Overall, 5 independent copies of the data will be analyzed. The estimates of the variables will be pooled according to Rubin rules. The pooled analysis will be presented. A complete case analysis will be performed as sensitivity analyses [60]. If >40% of the data are missing, we will use the observed data and report the extent of the missing data [59].

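### The missing-data section attaches two incompatible rules to the same trigger (more than 40% missing) and gives none for the 10% to 20% questionnaire loss the protocol expects

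*Protocol article*

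**What the plan says.** The Handling of Missing Data section of the protocol article gives these instructions, in this order:

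- Imputation trigger: "If >40% of the missing data in the data set occur, multiple imputation by the chained equations method in R will be used".
- Number of imputed data sets: "Overall, 5 independent copies of the data will be analyzed", with estimates combined by Rubin's rules.
- Main result under that rule: "The pooled analysis will be presented".
- Role of complete cases: "A complete case analysis will be performed as sensitivity analyses".
- Closing rule: "If >40% of the data are missing, we will use the observed data and report the extent of the missing data".

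The Sample Size section states the loss the authors expect: "We assume a 10% to 20% loss to follow-up (ie, not completing the questionnaires"). To allow for it, "the total sample size per group will be at least 150".

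**The concern.** The first and last instructions share a trigger and name different main analyses. A statistician facing a variable with more than 40% missing could not follow both. A statistician facing the expected amount of missing data would find no instruction at all.

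This matters more here than in a randomised trial. Groups are formed by patient and family preference, so the comparison depends on covariate adjustment. The Discussion treats comparison of many prognostic variables, social isolation among them, as essential. Under Data Collection Methods, social isolation (Friendship scale) and the socioeconomic variables come from patients' own answers. If those are incomplete, the handling of missing data decides which patients enter the adjusted models, including the adjusted model for readmission.

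The timing adds to this. The Results section says follow-up ended in May 2022 and publication was planned for the end of 2023. A rule that can be read either way allows the choice between imputed and observed data to be made with the data in hand.

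**Working it through.** The article states no figure to reproduce on this point. The check sets the rules beside the expected loss.

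**Inputs**
- Threshold in both rules: more than 40% missing (Handling of Missing Data).
- Expected loss: 10% to 20%, defined as uncompleted questionnaires (Sample Size).
- Planned size: at least 150 per group (Sample Size).
- Source of readmission and complication data: the electronic patient record (Table 2, follow-up after discharge).

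**Step 1: what applies on each side of the threshold**

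| Proportion missing | First rule | Closing rule | Result |
|---|---|---|---|
| More than 40% | Impute, present pooled result | Observed data only, report extent | Two incompatible main analyses |
| 40% or less | Silent | Silent | No main analysis defined |

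The complete-case sentence does not reconcile the two rules. It follows the imputation and pooling sentences and assigns complete cases a sensitivity role only.

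**Step 2: where the expected loss falls**
- 10% of 150 = 15 missing, 135 left per group.
- 20% of 150 = 30 missing, 120 left per group.
- 40% of 150 = 60 missing.

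The whole expected range of 15 to 30 lies below 60, in the row with no rule.

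**Step 3: is the denominator fixed?**
The first sentence counts missing data in the data set; the last speaks of the data being missing. Neither says whether the percentage is per variable, per outcome or overall. One might try to reconcile the rules by giving each a different denominator, but the text does not do so. The row at or below 40% would still be empty.

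**Step 4: which analyses are exposed**
- Questionnaire outcomes: EQ-5D-5L, HADS, and caregiver burden and well-being. These are directly exposed.
- Questionnaire-based confounders: socioeconomic data and the Friendship scale. These are exposed, and through them so are the adjusted models, the primary one included.
- Sleep quality, Delirium Observation Scale and mobility (AMEXO) scores over the first 5 days: analysed with a mixed model, which can use incomplete repeated measures. Less exposed.
- Readmissions and complications: taken from the patient record, as are most clinical baseline variables. Less exposed.

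**The case against.** The best defence is that this is a single wrong sign with a visible intent. The section presents the pooled imputed result, demotes complete cases to a sensitivity analysis, and then switches to observed data above 40%. That sequence makes sense if the first trigger was meant to read 40% or less. As an account of the cause, this is probably right. It does not remove the error: the article nowhere states the intended reading, and no other section resolves it. Other inequality signs in the article read correctly, so a fault in text extraction is unlikely. Nor is this a detail left to a fuller plan, since the rule is stated and contradicts itself.

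Four stronger readings are tempting and are not supported:

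- **That the plan prescribes complete-case analysis for the expected loss.** At or below 40% the text is silent. Ordinary regression software would drop incomplete records if nothing were done, but that is an inference and not a stated plan.
- **That a large, known share of patients would drop out of the adjusted models.** The article gives no missingness rates for covariates. If 20 covariates were each 2% missing (both figures assumed), the loss would be 2% with complete overlap, 1 − 0.98^20 = 33% with independence, and 20 × 2% = 40% with no overlap. A patient who skips a questionnaire misses all its items together, which pulls towards the low end. The range is too wide to carry the point.
- **That the primary outcome loses 10% to 20%.** That loss is defined by questionnaires, and readmission is taken from the patient record.
- **That five imputations are an error.** Relative efficiency is 1/(1 + FMI/m), where FMI is the fraction of missing information and m the number of imputations. At an assumed FMI of 0.4, m = 5 gives 1/1.08 = 93% and m = 40 gives 1/1.01 = 99%. The cost of m = 5 against unlimited imputations is √1.08, about 4% on the standard error. At an assumed FMI of 0.1 to 0.2, m = 5 gives 98% to 96%. More imputations are a reasonable preference, no more.

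**Conclusion.** Wrong as written. Above 40% missing, the section requires two mutually exclusive main analyses. At or below 40%, which covers all of the expected 15 to 30 patients per group, it requires none. This conclusion rests on the article's text and its own 10% to 20%, with no outside assumption.

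The reach is limited. Questionnaire outcomes and questionnaire-based confounders carry most of it; the primary analysis is touched through those confounders, while the readmission data are less exposed. The size of any bias or loss of precision cannot be derived from the article. That the first inequality was reversed is the most plausible explanation, but it remains an inference.

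**What to change.** Rewrite the section so that each side of the threshold has one rule:

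1. Up to 40% missing: multiple imputation by chained equations is the main analysis, pooled by Rubin's rules, with complete case as the sensitivity analysis.
2. More than 40% missing: observed data only, with the extent of missing data reported, as the closing sentence already says.
3. State that the percentage is counted per variable.
4. Because follow-up has ended, date the correction and document that it was made before any outcome analysis. If outcomes have already been analysed, say so.

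This keeps both procedures the authors described and covers the loss they expect. Using more than five imputations is optional. The cost is a few lines of wording, a dated record and negligible computing time; no new data are needed.

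### The number of imputed data sets is fixed at 5 whatever the amount missing; more would make borderline questionnaire results reproducible at almost no cost

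*Protocol article*

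**What the plan says.** The Handling of Missing Data section of the protocol article names chained equations as the method and sets the number of imputations: "Overall, 5 independent copies of the data will be analyzed". Pooling follows: "The estimates of the variables will be pooled according to Rubin rules". The imputed result is the main one: "The pooled analysis will be presented. A complete case analysis will be performed as sensitivity analyses".

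The same paragraph gives one threshold two opposite consequences. It opens with "If >40% of the missing data in the data set occur, multiple imputation by the chained equations method in R will be used" and closes with "If >40% of the data are missing, we will use the observed data and report the extent of the missing data".

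Under Statistical Methods, Outcomes, results are read against a two-sided criterion: a P "value ≤.05 will be considered statistically significant". The Sample Size section gives the loss that is expected: "We assume a 10% to 20% loss to follow-up (ie, not completing the questionnaires". Table 2 (Study Procedure) takes readmissions and complications from the electronic patient record.

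**The concern.** With 5 imputations, the between-imputation variance is estimated on 4 degrees of freedom. The pooled standard error, interval and P value then carry simulation noise, which comes from the random draws of the imputation and not from the patients. The noise grows with the fraction of missing information, but the stated number of imputations does not respond to it.

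Because the pooled analysis is the one presented and is judged against .05, two analysts following the same plan could report different verdicts on a borderline outcome. Intervals are also somewhat wider than the data require.

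**Working it through.** **Inputs.** From the article: m = 5 and the 40% threshold (Handling of Missing Data), two-sided .05 (Statistical Methods, Outcomes), 10–20% expected loss, 150 per group, and readmission rates of 20% and 35% (Sample Size). The article gives no derivation for m = 5, so there is no plan figure to reproduce. FMI is not in the article. It is assumed to be close to the missing rate and is shown over a range.

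**Step 1: closed-form noise.**
- Coefficient of variation (CV) of the pooled SE = FMI × √(0.5/(m − 1)). With m = 5 the root is √0.125 = 0.354.
- Reference df = (m − 1)/FMI².
- Interval width relative to many imputations = √(1 + FMI/m) × t(df)/1.96.

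| FMI | CV of SE, m = 5 | df | Width ratio |
|---|---|---|---|
| 0.1 | 0.1 × 0.354 = 3.5% | 4/0.01 = 400 | √1.02 × 1.966/1.96 = 1.013 |
| 0.2 | 0.2 × 0.354 = 7.1% | 4/0.04 = 100 | √1.04 × 1.984/1.96 = 1.032 |
| 0.4 | 0.4 × 0.354 = 14.1% | 4/0.16 = 25 | √1.08 × 2.06/1.96 = 1.09 |

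At FMI 0.4 with m = 40, the CV is 0.4 × √(0.5/39) = 4.5%.

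**Step 2: Monte Carlo check of Rubin's rules** (Barnard-Rubin df, 400,000 draws per setting). With m = 5 the CV of the SE is 4.1%, 7.9% and 14.9% at FMI 0.1, 0.2 and 0.4, and 18.4% at FMI 0.5. With m = 40 it is 4.6% at FMI 0.4. The simulation noise in the estimate itself is √(FMI/m) in SE units: √(0.4/5) = 0.28 with m = 5, and √(0.4/40) = 0.10 with m = 40.

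At FMI 0.4, take a result whose P would be .028 with unlimited imputations. With m = 5, 95% of seeds give P between .003 and .189, and 57% of seeds declare it significant. With m = 40 the range is .015 to .058, and 93% declare it significant.

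**Step 3: chance that two seeds disagree on P ≤ .05**, with 150 per arm.
- Logistic model: 35% against 20%, one assumed covariate, outcome missing completely at random.
- Continuous outcome: assumed effect 0.3 SD, baseline correlation 0.5.

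| Missing | Logistic, m = 5 | Logistic, m = 40 | Continuous, m = 5 | Continuous, m = 40 |
|---|---|---|---|---|
| 10% | 7% | 3% | not run | not run |
| 20% | 14% | 4% | 11% | 3.5% |
| 40% | 18% | 6% | 22% | 5% |

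Both settings lie near the border. At 40% missing, 90 per arm remain. The continuous effect then has an expected z of 0.3/√(2/90) = 2.0 unadjusted. The logistic setting has roughly 0.15/√((0.35 × 0.65 + 0.20 × 0.80)/90) = 2.3. Away from the border the problem fades: with m = 5 and FMI 0.2, two seeds disagree 0.5% of the time when the unlimited-m P is .003, and essentially never when it is .32.

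**Step 4: how many imputations are needed.** For a CV of the SE of at most 5%, m = 1 + 0.5 × (FMI/0.05)². This gives 3, 9, 33 and 51 at FMI 0.1, 0.2, 0.4 and 0.5.

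**Step 5: the contradictory trigger.** If imputation applies up to 40% missing, m = 5 covers the expected 10–20% loss, where the noise is mild, and runs up to the 40% bound. If it applies only above 40%, as first printed, it does not run at the expected loss. When it does run, the noise is at its largest. Resolving the threshold does not by itself make m = 5 suitable.

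**The case against.** The strongest reply is that the large figures belong to an upper bound. The 40% is a threshold; the expected loss is 10–20%. At FMI 0.1–0.2 the SE noise is about 4–8%, the interval is only 1–3% wider, and 3 to 9 imputations would meet the 5% target. FMI can also fall below the missing rate when repeated measurements inform the imputation: Table 1 has EQ-5D-5L and HADS at baseline, discharge and two follow-ups. A complete-case sensitivity analysis, free of seed noise, is planned. Relative efficiency of the estimate at FMI 0.4 is still 1/(1 + 0.4/5) = 0.926. All of this stands and keeps the point small.

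Two stronger readings are tempting. A reader might infer that the trial's main verdict hangs on the seed. The documents do not support that: readmissions come from the patient record, whereas the anticipated loss is of questionnaires. Imputed covariates, such as the Friendship scale named as a potential confounder, could reach the model in "For the primary outcome (ie, unplanned readmissions up to 30 days after surgery), we will conduct logistic regression analyses". A missing covariate usually costs the treatment coefficient far less information than a missing outcome, so FMI 0.4 is not the relevant value there.

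A reader might also infer that verdicts in general would flip between analysts. The 11–22% rates arise in settings placed near P = .05 and do not carry over to clear results.

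That the article does not mention recording a seed is no defect, since such detail normally sits in the analysis plan or code.

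**Conclusion.** The point holds as an inexpensive improvement. It does not threaten the trial's validity. Five imputations is a stated number, unrelated to the amount missing, in a section that contemplates missingness up to 40% or, as printed, above it. The cost is reproducibility and a little precision: SE noise of about 4%, 7–8% and 14–15%, and intervals about 1%, 3% and 9% wider, at FMI 0.1, 0.2 and 0.4. Verdicts are exposed only for results near .05. There is no bias in the point estimate.

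The outcomes concerned are mainly EQ-5D-5L, HADS, and caregiver burden and well-being; the primary outcome is affected at most through imputed covariates. The sizes rest on FMI being close to the missing rate, and the disagreement rates rest on simulated effects near the border.

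**What to change.** Replace the fixed 5 with a number of imputations at least equal to the percentage of patients with incomplete data, which is about 40 at the 40% bound. A flat 40 is also acceptable and simpler to state, although it exceeds what the expected 10–20% loss needs. In the same edit, reconcile the two >40% sentences so that it is clear at what level of missingness imputation is used. No new data are needed; the cost is a short text change and a little computing time.
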